### Study procedures

#### Data collection: clinic level

At baseline, all clinics (those receiving training and those receiving no training) complete a clinician (e.g., physicians, nurses) or clinic support staff (e.g., receptionists, clerks) survey assessing (after providing informed consent) SRH knowledge and service provision, attitudes toward PrEP and AGYW seeking PrEP, and observations of stigmatizing and discriminatory behavior in their clinic toward AGYW seeking services for SRH, HIV, and PrEP (see Clinician Questionnaire & Support Staff Questionnaire in Supplementary Files 1 & 2). This survey is re-administered at 4- and 8-months post baseline. Given the staff turnover and availability and to ensure to anonymity, staff surveys are not linked across time points; consequently, changes at the clinic level are assessed. Clinic support staff surveys have been translated into a local language, Setswana, for easier comprehension. A clinical audit is also being conducted at baseline and 4-month and 8-month follow-up by research study staff to collect information on service utilization, including the number of AGYW receiving health services (including HIV, birth control, and antenatal care) from clinical records; PrEP prescriptions from pharmacy and study nurse records; availability of birth control methods; presence of clinic guidelines and standards of practice for serving sexually active AGYW; working hours that are convenient for AGYW, as well as adequate staff to provide youth friendly services. This audit is conducted across all study clinics.

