#### Intake assessment

After consenting/assenting, participants also sign a release of medical records permitting the release of information on their SRH, PrEP screening and monitoring results, and other referrals and care pertinent to the study.

Participants take a breathalyzer test to detect recent alcohol use (conducted earlier in the appointment because of the limited detection window for alcohol breath scans) and provide urine for drug screening, locator information is collected, and a photograph of the participant is taken to identify the participant for subsequent appointments. This photo is returned or shredded at the final appointment. The participant then completes a baseline questionnaire on a computer tablet via audio computer-assisted self-interview (ACASI) in either English or Setswana (see AGYW Health CoOp Questionnaire in Supplementary File 3). Trained field staff are available to assist the participant at any time and provide referrals based on prompts related to self-reported violence, symptoms of psychological distress, or suicidal ideation experienced in the past 3 months that are triggered as the participant completes the questionnaire. The questionnaire is derived from components of the youth-specific modification of the Revised Risk Behavior Assessment (RRBA) [54], which has been adapted and modified for many studies in South Africa. The modified RRBA for this study contains sections on PrEP knowledge, contraception and other SRH services access and utilization, sexual communication, STI symptoms, alcohol and other drug use, relationship equity and sexual control, economic dependence, personal agency, psychological distress, victimization, and peers and social support. After completing the questionnaire, urine drug screening results are provided to assess the recent use of amphetamine, methamphetamine, benzodiazepine, cocaine, marijuana, opioids, and MDMA. These screening tests are repeated at 3-, 6-, and 9-month follow-up assessments.

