#### Outcomes

The clinic-level primary outcomes for this study include clinic staff attitudes and environment, observed discrimination, and stigmatizing avoidance behaviors toward AGYW, as measured by staff surveys and the clinic audits. The AGYW-level primary outcomes include the level of PrEP readiness, uptake, and adherence (as measured by self-report and DBS), and SRH uptake. The AGYW-level secondary outcomes include frequency of substance use, as measured by the RRBA and biological drug screening and breathalyzer tests to assess recent alcohol use; GBV, assessed through self-reported experiences of emotional, physical and sexual abuse; sexual risk as measured by condomless sex, impaired sex, other sex partners; self-reported frequency of experienced stigma.

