#### Sample size and power

For the AGYW analyses, the total sample size and number of clusters (clinic catchment areas) were selected to ensure sufficient power to detect meaningful differences in our primary outcomes, while also balancing considerations tied to reducing possible contamination (exposure to the intervention in control clusters) and implementation feasibility with a set number of clinics in the study area. Sample size estimates for tests of two proportions in a cluster-randomized design [56] were conducted for a 2-sided test with significance level of 0.05, power of .80, and intra-cluster correlation of 0.01 (based on our team’s past research in Cape Town communities), assuming 10% attrition over the 9-month follow-up period [52, 57]. This was not adjusted for multiple comparisons. Based on these parameters and calculations, the study sample includes 12 clusters (defined as clinics and their catchment areas), with a total sample size of 900 AGYW enrolled, 75 per cluster (clinic catchment area). This sample was chosen to ensure that meaningful differences in the primary outcomes of PrEP readiness, uptake, and adherence between groups would be detectable. We are powered to detect a difference between 9 to 13% in primary outcomes. Power analyses were first conducted in PASS software [58] and were refined in Stata [59] (see PrEPARE Additional Power Calculation Information in Supplementary File 4).

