From the AGYW outcomes, it is hypothesized that AGYW enrolled from clinics who received clinic-level S&D reduction training will have higher PrEP and SRH utilization than AGYW enrolled from clinics that did not receive training. AGYW enrolled from clinics that are randomized to receive the YWHC intervention will have higher PrEP readiness, uptake and adherence than those enrolled from clinics that are randomized to PrEP and SRH provision only. AGYW enrolled from communities in clinic catchment areas that are randomized to receive the YWHC will report less HIV-related risk at follow-up (e.g., GBV, substance use, condomless sex) than those enrolled from clinics that are randomized to PrEP and SRH provision only.

Missing data in terms of data management may occur because of nonresponse and study attrition. We will analyze differential attrition in relation to participants’ key demographic characteristics. Based on our prior research conducted in South Africa with AGYW who engage in sex risk behaviors, we estimate an average retention rate of 90% over the repeated follow-ups [19, 37, 62]. We will address missingness by including demographic covariates that will serve as proxies for dropout and by conducting a sensitivity analysis.

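### Missing uptake data are handled through demographics alone, which leaves the GEE open to bias if PrEP-related dropout differs by arm; planned dispensing data could close part of the gap

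*Protocol article*

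**What the plan says.** All references are to the protocol article.

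- **Missing data (Analysis, AGYW level).** The stated method is: "We will address missingness by including demographic covariates that will serve as proxies for dropout". The same sentence adds a sensitivity analysis, without describing it. Differential attrition is to be related to participants' main demographic features; neither study condition nor PrEP use is named. On the amount, "we estimate an average retention rate of 90% over the repeated follow-ups". Sample size and power uses the matching figure, "assuming 10% attrition over the 9-month follow-up period".
- **Uptake (same section).** Uptake is any use of PrEP, taken both within 3 months and at any point over 9 months. The analysis is by intention to treat, using a GEE with logit link and exchangeable correlation, with both intervention factors in the model.
- **Measurement.** Outcomes lists readiness, "uptake, and adherence (as measured by self-report and DBS"). Under Follow-up assessments, DBS are taken only from attending women who say they are on PrEP.
- **Records.** The AGYW-level analysis plans to combine clinic and pharmacy dispensing data with self-report, to study months of use and discontinuation. At intake, "participants also sign a release of medical records", which covers PrEP screening and monitoring. The clinic audit separately gathers "PrEP prescriptions from pharmacy and study nurse records".
- **Contact by arm.** YWHC women are checked on at least monthly, and those on PrEP receive navigation and refill reminders. Linkage in the control groups is followed up at the 3-month visit (Sexual and reproductive health services; YWHC workshops; PrEP navigation after PrEP initiation).

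**The concern.** An analysis of attenders adjusted for condition and demographics assumes that, given those variables, staying in the study is unrelated to PrEP use, or at least related to it in the same way in every arm. The design gives reason to doubt this. In the YWHC arms a woman on PrEP is contacted for adherence support and refills, and a woman not on PrEP still gets check-ins. In the control arms neither applies. Demographic variables do not carry that information.

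The 9-month definition adds an asymmetry. A woman who reports use at 3 months and then leaves is already a known user. A woman who has not started by 3 months and then leaves is undetermined, because PrEP may be started at any time. If undetermined women are dropped, observed uptake is too high, and more so in the arm that loses more of them.

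At stake is the estimated effect on a primary outcome. The trial is sized for differences of 9 to 13 points, and about 10% of women are expected to be lost.

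**Working it through.** **1. The plan's own figure.** Inputs from Sample size and power: "2-sided test with significance level of 0.05, power of .80, and intra-cluster correlation of 0.01", 12 clusters, 75 women each, 10% attrition. Each factorial main effect compares 6 with 6 clinics.

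- Women per clinic after attrition: 75 × 0.9 = 67.5.
- Effective number per side: 6 × 67.5 / [1 + (67.5 − 1) × 0.01] = 405 / 1.665 = 243.2.
- Control rates are not given in the article, so a range is assumed. The difference detectable at 80% power (two proportions, normal approximation) is 8.9 points at a control rate of 10%, 11.1 at 20%, 12.2 at 30%, and 12.6 at 40% and 50%.

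The stated 9 to 13% is reproduced. The sample size is not in question.

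**2. When the odds ratio is biased.** Let r_u and r_n be the retention of users and non-users in an arm. The observed proportion is p·r_u / [p·r_u + (1 − p)·r_n], so the observed odds are the true odds times r_u/r_n. Therefore

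observed OR = true OR × (r_u/r_n in YWHC) / (r_u/r_n in control).

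If the ratio is the same in both arms, the odds ratio is unchanged. Check with 30% against 42.2% uptake and retention of 95% in users and 85% in non-users in both arms: the OR stays at 1.70, while the difference moves from 12.2 to 12.5 points. Bias in the OR needs a ratio that differs by arm.

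**3. Size under assumed retention.** None of the retention splits below is in the article, which gives only a 90% average.

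*Retention 95% in YWHC and 85% in control; uptake 40% in retained and 20% in lost women:*
- True YWHC: 0.95 × 0.40 + 0.05 × 0.20 = 0.39.
- True control: 0.85 × 0.40 + 0.15 × 0.20 = 0.37.
- Observed: 0.40 in both. A true difference of 2.0 points appears as 0.

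*The same with 5% uptake in lost women:*
- True YWHC: 0.38 + 0.05 × 0.05 = 0.3825.
- True control: 0.34 + 0.15 × 0.05 = 0.3475.
- A true difference of 3.5 points appears as 0.

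*10% dropout per arm, YWHC dropout unrelated to use, true rates 30% and 42.2%:*

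| Control dropout | Observed control | Observed difference | OR (true 1.70) | Power |
|---|---|---|---|---|
| All non-users | 0.30 / 0.90 = 0.333 | 8.8 points | 1.46 | 52% |
| Non-users leave twice as often as users | 0.314 | 10.8 points | 1.60 | 70% |

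For the second row, user dropout is x = 0.1 / (0.3 + 2 × 0.7) = 0.0588, and 0.3 × (1 − 0.0588) / 0.9 = 0.314. Across control rates of 10% to 50%, power in the all-non-users case runs from 67% to 35%.

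*Worst-case bounds* with 10% missing per arm are 0.9 × observed difference ± 10 points. For an observed 12.2 this is 1.0 to 21.0.

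**4. Precision, if records completed uptake for everyone.** Effective number per side: 450 / [1 + 74 × 0.01] = 450 / 1.74 = 258.6. The detectable difference scales by √(243.2 / 258.6) = 0.97, a gain of about 3% at most. Power at the step 1 differences goes from 80.0% to 82.4%.

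**The case against.** The case on the other side has several sound parts.

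- **A sensitivity analysis is planned.** Its form may be set out in an analysis plan that is not shown, so its lack of detail is no fault of the article. It does not alter the primary estimate, however, and the primary method is stated.
- **Condition is in the model.** Dropout that differs by arm alone is already conditioned on, and behavioural covariates may enter if they are unbalanced at baseline. A reader might infer that any link between dropout and PrEP use biases the GEE. Step 2 shows that this is too strong for the odds ratio.
- **The source for uptake is not exclusive.** In Outcomes, the parenthesis on self-report and DBS may qualify adherence only, and nothing rules out dispensing data for uptake. Nor are all of the expected 10% missing for 9-month uptake, because a woman who reported use at 3 or 6 months is already classified.
- **Complete records are not established.** A reader might infer that dispensing records give uptake for all 900 women. The audit in Data collection: clinic level is a clinic-level exercise at baseline, 4 and 8 months, and the article nowhere states that individual records are complete. The signed release, supply through the study clinic or roaming nurse, and the absence of a public roll-out make good coverage likely, but do not prove it.
- **Collecting pills is not use.** Replacing the endpoint with dispensing would trade missing data for misclassification. The documents give no ground to call the present definition wrong.
- **Adherence has its own model.** The planned mixed models with repeated measures already use earlier visits.

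What remains is narrower: the stated remedy cannot address PrEP-related dropout, contact differs by arm and PrEP status, and a relevant data source already in the plan is assigned only to other measures.

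**Conclusion.** The point holds for uptake in this limited form. Demographic proxies leave the logit GEE exposed if the association between PrEP use and dropout differs by arm. The design makes that plausible, though nothing in the article shows that it occurs. Arm proportions and the risk difference can shift without that condition.

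Under the assumed inputs the error is 2.0 to 3.5 points in the moderate cases. In the harsher case a true 12.2 points shrinks to 8.8. All of these examples attenuate a benefit of YWHC; a different dropout pattern could inflate it. The figures illustrate scale and are not forecasts.

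The documents do not support the stronger conclusions that the endpoint must be replaced, that the GEE is necessarily biased, or that the trial is undersized. The change is worth making before analysis because it is cheap and uses data already planned. The main gain is protection against bias; the gain in precision is minor.

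**What to change.** 1. **Uptake.** Keep any use of PrEP as the definition. State that participant-level clinic, pharmacy and study-nurse dispensing data will complete 3- and 9-month uptake for women without the visit data needed to classify them. Report the version based on self-report and DBS alone alongside.
2. **Outcomes that need a visit (readiness, DBS adherence).** Replace demographics alone with a missing-data model, for example multiple imputation, that includes condition, baseline values, earlier-visit outcomes and dispensing history.
3. **Attrition.** Tabulate it by arm and by PrEP history as well as by demographics.
4. **Sensitivity analysis.** Direct the one already planned at PrEP-related dropout that differs by arm.

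The cost is analysis-plan wording and linkage of records that participants have agreed to release. There are two drawbacks. Dispensing may count women who collected PrEP but never took it; comparing dispensing with self-report among attenders would show how often. The completeness of the records is not stated and must be checked, by clinic and arm, before the absence of a record is read as non-use.

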### Ethical approval

#### Full experimental protocol approval and amendments

The experimental phase of the study was approved by the South African Medical Association Research Ethics Committee (SAMAREC), which serves as the Institutional Review Board (IRB) of Record, in addition to the Tshwane District Health Research Committee and the Skills Development for Tshwane Municipal Clinics. Since receiving approval to conduct the full study, we amended the protocol to improve the study design and procedures. Table 3 summarizes these approvals.

**Table 3 Tab3:** Summary of Protocol Approval and Amendments

Date of approval	Protocol and Amendments
1/2019	Initial submission to conduct the experimental phase of the study
3/2019	Request for SAMAREC to be the IRB of Record
3/2019	Revised research protocol and supporting materials to prepare for the full study phase
4/2019	Amended full study research activities to allow for the provision of PrEP
7/2019	Addition of participant follow-up consent documents and the 3-month follow-up questionnaire
10/2019	Minor revisions to study screener and eligibility criteria to ensure participants are not currently enrolled in another HIV project and to the study protocol regarding follow-up on pregnancy outcomes of participants who become pregnant during the course of the study
11/2019	Reduced the number of clinic staff follow-up visits from 3 to 2 appointments—specifically, 4- and 8-month follow-up appointments
2/2020	Minor modifications to study documents and protocol to prevent co-enrollment of participants involved in other HIV studies in the Tshwane area
3/2020	Modification to allow project staff to complete at-home data entry of de-identified data, and the submission of a staff agreement of confidentiality for at-home data entry because of the COVID-19 lockdown
4/2020	Minor modifications to clinician and support staff follow-up questionnaires and consenting procedures
4/2020	Notification to the IRB of resumption of limited face-to-face appointment with study participants during the COVID-19 lockdown
4/2020	Submission of the COVID-19 questionnaire to be administered via telephone during the COVID-19 lockdown

With COVID-19, there have been barriers and disruptions to PrEP initiation and dispensing, which may alter some of the expected study outcomes, study activities and data collection. We attempted to address these unprecedented circumstances (as noted in Table 3) without compromising the rigor of the research design and ensuring that participants were able to stay on PrEP. Some of the strategies included getting personal protective equipment, ensuring a travel nurse was able to dispense PrEP, and when possible, providing refills longer than 30 days. We will be monitoring these circumstances as they are changing daily.

#### Dissemination

Study findings will be disseminated to participants, health care professionals, and other stakeholders through our established YAB and CCB, program newsletter, journal articles, conference presentations and also other targeted dissemination channels.

## Discussion

This article describes the study protocol for a research study aimed at evaluating the impact of a stigma and discrimination reduction training program for clinic staff and the efficacy of a multilevel HIV prevention strategy that addresses young women’s empowerment to include substance use, sexual risk, and GBV; and access to and use of SRH and PrEP.

The UNAIDS Fast-Track Approach agenda, which drives the 95–95-95 goals for HIV prevention and treatment by 2030, includes ambitious targets for reducing new HIV infections and achieving zero discrimination, including in healthcare settings [1]. To meet this agenda, we must reduce the incidence of HIV among AGYW who are the least likely to have access to HIV prevention, testing, and treatment services but carry the greatest burden of HIV. Furthermore, although PrEP is safe and is a highly effective prevention method, especially among individuals at high risk of HIV acquisition, PrEP uptake and adherence remains low among certain high priority populations, particularly AGYW. This is the first study of its kind in South Africa to attempt to address structural S&D in public health clinics as a way to improve PrEP readiness, uptake, and adherence among this population and in turn reduce HIV burden.

The study comprises some notable innovations: (1) developing a partnership with the South African Department of Health to reduce S&D by clinic staff; (2) engaging the study’s YAB and the CCB in the adaptation of the YWHC (YAB) and the S&D (CCB) interventions, study marketing materials (YAB), S&D reduction training (YAB) as stakeholders to share their voices, and the regular meetings. This is an important step towards involving community members in the dissemination and implementation of HIV-prevention structural interventions. Support for structural changes may increase when the people whom the intervention is likely to affect participate in the process [63]; and (3) other contextual factors, such as GBV and substance use, and using an evidence-based, gender-focused approach are addressed. Additionally, partnering with the NDoH and the public health clinics is facilitating capacity building through the standardized PrEP provider training that will be required when PrEP provision is scaled up to a population level. Because this study is being conducted in collaboration with public health clinics, it may bring to light challenges that need to be addressed prior to integrating PrEP delivery into public health facilities, such as workload, the need for task shifting or sharing, and the need to enhance PrEP’s general acceptance in usual care settings.

Few interventions currently exist that address the multiple levels of the psychosocial and community barriers that prevent AGYW from accessing healthcare services. The adapted YWHC provides a more comprehensive HIV prevention toolkit with PrEP and reproductive health as next generation science. If found to be efficacious, the YWHC plus addressing the structural S&D may help reduce barriers to HIV prevention among a key population with the greatest incidence—offering more hope for an HIV-free generation of young women.

## Trial status

Recruiting.

## Data Availability

The study is currently enrolling; therefore, data collection is ongoing. The datasets used and/or analyzed during the current study will be available from the corresponding principal investigator when outcomes and publications are complete.

## Abbreviations

ACASI: Audio computer-assisted self-interviewing
AE: Adverse event
AGYW: Adolescent girls and young women
ARV: Antiretroviral
CCB: Community Collaborative Board
DBS: Dried blood spots
DD: Difference-in-differences
DREAMS: Determined, Resilient, Empowered, AIDS-free, Mentored and Safe
DSMB: Data and Safety Monitoring Board
DSMP: Data and Safety Monitoring Plan
FTC: Emtricitabine
GBV: Gender-based violence
GEE: Generalized estimating equations
HAST: HIV/AIDS, STI, and TB
HBV: Hepatitis B virus
HPLC: High-performance liquid chromatography
HPP: Health Policy Project
IRB: Institutional Review Board
MDMA: 3,4-Methylenedioxymethamphetamine
MDR-TB: Multi-drug resistant tuberculosis
NDoH: National Department of Health
PID: Participant identification number
PrEP: Pre-exposure prophylaxis
PrEPARE: *PRevention, Empowering, and PRotEcting*
QMP: Quality Management Plan
RRBA: Revised Risk Behavior Assessment
SAE: Serious adverse event
SAMAREC: South African Medical Association Research Ethics Committee
S&D: Stigma and discrimination
SRH: Sexual and reproductive health
STI: Sexually transmitted infection
TB: Tuberculosis
TDF: Tenofovir disoproxil fumarate
TFV-DP: Tenofovir diphosphate
UNAIDS: Joint United Nations Programme on HIV/AIDS
WBOT: Ward-based outreach team
WHC: Women’s Health CoOp
YAB: Youth Advisory Board
YWHC: Young Women’s Health CoOp
